### Data Analyses

Blinded outcome assessment will be undertaken for all analyses of primary and secondary outcome measures. Data will be analysed using Stata [51]. Intention-to-treat analysis will applied [26].

To examine potential response bias, demographic characteristics for eligible consenting and non-consenting patients will be compared using the chi-square test for categorical variables (sex, stroke sub-type, and stroke severity) and the t-test (or a non-parametric equivalent) for the continuous variable of age.

For all patient-related outcome analyses, we will use cluster-specific methods. Dichotomous outcomes (death or disability [mRS ≥2] at 90 days; swallowing screen within 24 hours of admission) will be compared between intervention and control groups using the chi-square test. Continuous outcomes – level of disability (mRS score), dependency (Barthel Index), health status (MCS and PCS of SF-36), improved glycaemic control, and improved temperature control – will be compared between the two intervention groups using the t-test. The survey (svy) commands in Stata will be used to adjust for clustering of patients within ASUs. Multilevel modelling (logistic or linear as appropriate) will be used to compare primary outcomes – death or disability (mRS or ≥2) at 90 days, level of disability (mRS score), dependency (Barthel Index), and health status (MCS and PCS of SF-36) – between groups while adjusting for potential confounders or effect modifiers and for the cluster study design. These analyses will be undertaken in the Stata statistical package [51].

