#### Other Clinical Measures

In addition, the following clinical measures will be used to describe and compare the groups and considered as potential confounders:

1. Stroke subtype: Using the Oxfordshire Community Stroke Project (OCSP) Classification [47], a four item scale that classifies strokes using explicit criteria as either lacunar infarcts, total anterior circulation infarcts, partial anterior circulation infarcts, or posterior circulation infarcts.

2. Stroke severity: Using the Scandinavian Stroke Scale (SSS)[48], a measure of stroke severity involving assessment of the following parameters: consciousness, eye movement, motor power – arm, hand, leg, orientation, speech, facial palsy and gait to be measured on admission. Score range from zero to 58; the Los Angeles Motor Scale (LAMS), a motor deficit score ranging from zero (least affected) to ten (most affected) for bilateral weakness and zero to five in patients with unilateral weakness [49,50].

3. level of pre-morbid disability using the mRS [42,43]

4. demographic variables: age, sex, date of hospital admission, and length of stay

For missing data, patient clinical data will be obtained from the TASC database. Patients themselves will already have agreed to allow access to these data as part of the study consent. For hospitals that do not collect TASC data, stroke severity, stroke sub-type, level of pre-morbid mRS, and demographic variables will be prospectively manually collected from patient medical records by CRAs at each participating site following patient recruitment.

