### Sample Size

TASC data from January 2003 to May 2005 demonstrated that 35% of patients had a mRS ≥2 at hospital discharge, and the mean hospital discharge mRS was 2, with a standard deviation of 2. A sample of 250 per group would allow detection of a difference between groups of 12% (35% versus 23%) for the proportion of patients with death or disability (≥2 on the mRS) and a clinically meaningful difference in mean mRS of 0.5 (from 2 to 1.5, equivalent to a 25% change in mean score) with 80% power and a 5% (two-sided) significance level. This sample would also allow detection of differences between groups of at least 13% for binary outcomes and one-quarter of a standard deviation for continuous outcomes, with 80% power and a 5% (two-sided) significance level. Assuming a loss to follow-up of 10%, an effective sample size of 280 participants per group is required to be recruited. These calculations assume independent observations. We devised a table to demonstrate statistical power according to various defensible estimates of intra-cluster correlation co-efficients (ICCs) for these two patient outcomes (Table 2). Estimated ICCs range from 0.01 to 0.03 [52]. We anticipate a design effect of 1.85, thus aim to recruit 520 patients per group (1,040 in total).

**Table 2 T2:** Effective sample size, assuming different magnitudes of intracluster correlation (ICC)^

**ICC**	**Design Effect**	**Number of patients per group**	**Total number of patients required**
0	1	280	560
0.01	1.4	400	800
0.015	1.85	520	1040
0.02	2.6	730	1460
0.03	4.4	1230	2460

^ 80% power at alpha = 0.05; nine ACU's per group; adjusted for loss to follow-up of 10%

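### The consent check compares stroke severity, an ordered score, by a chi-square test that ignores order, which makes it less sensitive to a systematic severity shift (minor)

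*Protocol article*

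**What the plan says.** The second paragraph of Data Analyses sets up the check: "To examine potential response bias, demographic characteristics for eligible consenting and non-consenting patients will be compared". It assigns a test to each variable. Three are "compared using the chi-square test for categorical variables (sex, stroke sub-type, and stroke severity"; the fourth is given "the t-test (or a non-parametric equivalent) for the continuous variable of age".

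Other Clinical Measures, item 2, describes how severity is recorded. The first instrument is the SSS, with "Score range from zero to 58". The second instrument, LAMS (Los Angeles Motor Scale), is described as "a motor deficit score ranging from zero (least affected) to ten (most affected) for bilateral weakness and zero to five" for one-sided weakness. Both are ordered numeric scores.

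The article prints no severity bands, names no test for ordered categories, and does not say which of the two instruments the consent check uses.

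**The concern.** The two sections do not fit together well. One measures severity on an ordered score; the other handles it like sex, where the categories have no order. A Pearson chi-square statistic is unchanged if the categories are shuffled, so it spreads its power over every possible pattern of difference. The response bias most naturally feared has a direction: patients who decline, or whose families decline, are on the whole more or less severely affected than those who agree.

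The article is also uneven in its own practice. In the next paragraph of Data Analyses it treats the modified Rankin score, which runs only from zero to six, as continuous and compares it by t-test.

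At stake is how much reassurance a non-significant result can give. Severity is among the potential confounders listed under Other Clinical Measures, so a real severity difference between consenters and non-consenters bears on how far the enrolled patients represent those eligible.

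**Working it through.** The plan gives no sample size, power or effect size for this check, so there is no figure of its own to reproduce. The question is how much sensitivity the named test gives up.

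**Inputs from the article**
- Consenters: n₁ = 1,040, the planned total (Sample Size).
- Two-sided 5% level. Sample Size states it for the outcomes; carrying it over to this check is an assumption.
- One quarter of an SD is the article's yardstick for continuous outcomes. It is used here only as the top of an illustrative range.

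**Assumptions not in the article**
- Non-consenters: n₂ = 115, 260 or 450, that is refusal of about 10% (115/1,155), 20% (260/1,300) or 30% (450/1,490).
- A normal severity score shifted by 0.15 to 0.25 SD, no clustering, and four bands cut at the consenters' quartiles.

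**Main case: n₂ = 260, shift 0.20 SD**

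1. *Test on the score.* z = 0.20 / √(1/1,040 + 1/260) = 0.20 / 0.0693 = 2.88. Power = Φ(2.88 − 1.96) = Φ(0.92) ≈ 0.82.

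2. *Chi-square on four bands.* Consenters have 0.25 in each band. Non-consenters have 0.191, 0.230, 0.262 and 0.318. The noncentrality is λ = (n₁n₂/N) Σ (pⱼ − qⱼ)²/p̄ⱼ, with n₁n₂/N = 1,040 × 260/1,300 = 208 and p̄ⱼ the pooled proportion. The sum is about 0.0342, so λ ≈ 7.1. With 3 degrees of freedom and critical value 7.81, power ≈ 0.60.

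3. *Trend test on the same four bands, scored 0 to 3.* The mean band score differs by 0.206 and the pooled variance is 1.25. z = 0.206 / √(1.25 × (1/1,040 + 1/260)) = 2.65. Power = Φ(0.69) ≈ 0.76.

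Simulation of the same case agrees: 59% for chi-square on four bands, 76% for a rank test on those bands, 79% for a rank test on the score and 81% for a t-test.

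**Across the assumed range (same formulas)**

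| Non-consenters | Shift (SD) | Chi-square, 4 bands | Trend, 4 bands | Test on score |
|---|---|---|---|---|
| 115 | 0.15 | 0.19 | 0.29 | 0.33 |
| 115 | 0.25 | 0.48 | 0.65 | 0.72 |
| 260 | 0.20 | 0.60 | 0.76 | 0.82 |
| 260 | 0.25 | 0.81 | 0.91 | 0.95 |
| 450 | 0.20 | 0.79 | 0.90 | 0.94 |
| 450 | 0.25 | 0.94 | 0.98 | 0.99 |

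The chi-square has the lowest power in every row. In the last row the gap is only 4 to 5 points.

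**The opposite pattern: same mean, wider spread.** Suppose refusal is concentrated at both ends of severity, so that non-consenters have the same mean but an SD 1.3 times larger (1,040 against 260). Their band proportions become 0.302, 0.198, 0.198 and 0.302, so λ ≈ 9.0 and chi-square power ≈ 0.71; simulation gave 73%. In simulation the t-test had 5% power and the rank-sum test 7%. At 1.2 times the SD the simulated figures were 40%, 5% and 6%.

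**The case against.** The strongest reply is that calling severity categorical most naturally means severity categories, and that an article may leave their definition to a fuller plan. Chi-square on bands is then a valid test with the correct error rate, and the point reduces to a choice between valid tests. This largely stands. A reader might infer that the raw 0-to-58 score will be cross-tabulated, which would cost far more power; nothing in the article says so, and the size given here does not rest on it. What survives is that, even with bands, the named test ignores their order, and a test that uses it regains most of the lost power.

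Second, no ordered test is better against every alternative. If refusal is concentrated at both extremes, the chi-square can see it and a t-test or rank test hardly can. This stands in full: the change is a trade-off, and the fix has to cover it.

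Third, a full SSS may not exist for non-consenters. Access to medical records and to the clinical database is described under Patient recruitment as something participants agree to, and at hospitals without that database severity is collected after recruitment. This stands too, so the fix must also work with bands. Since LAMS has different ranges for bilateral and unilateral weakness, a simple mean comparison of it could mix scales.

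Fourth, the article does not rank severity among the prognostic factors, and it does not say how a non-significant result would be read. Calling severity the strongest factor, or predicting a false claim of no bias, goes beyond the text.

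**Conclusion.** The point holds as a minor, inexpensive improvement. The article measures severity on ordered scores and then names a test that discards the order, which makes the consent check less sensitive to a systematic severity shift. In the main case power is about 59–60% for chi-square on four bands and about 76–82% for tests that use the order, a loss of roughly 16 to 22 points. The loss falls to about 4–5 points for a larger shift with more non-consenters. These sizes rest on an assumed refusal rate, shift and score distribution, and on ignoring clustering. The direction for a one-way shift was the same in every scenario run.

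A reader might infer that the trial's main results are at risk. The documents do not support that. The check describes who consented; it does not enter the randomised comparison, its type I error or the sample size. Potential confounders, severity among them, are handled separately in the multilevel models.

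**What to change.** In the response-bias paragraph of Data Analyses, take stroke severity out of the chi-square list and state that it will be compared by a test that uses its order:

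- where SSS scores are held for both consenters and non-consenters, a rank-sum test or t-test on the SSS;
- where only severity bands are available, a rank-sum or trend test on the bands, with the bands defined in advance.

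Report the size of the difference with its 95% CI, and name the instrument used. Keep chi-square for sex and stroke sub-type. Because an ordered test is nearly blind to a pure difference in spread, also tabulate or plot the severity distribution by consent status.

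The cost is a sentence or two of analysis wording and one descriptive display. No data are needed beyond whatever severity information the planned check already requires for non-consenters.

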#### Patient recruitment

##### Patient inclusion and exclusion criteria

To obtain baseline outcome and care data at the patient level, we will recruit a consecutive sample of English-speaking patients, aged >18 years, presenting within 48 hours of onset of symptoms who are given a clinical diagnosis of ischaemic stroke or intracerebral haemorrhage that is subsequently confirmed by CT imaging. These clinical criteria are specific and standard for stroke research. Patients will be excluded if they present to the ASU 48 hours or greater following onset of symptoms, have non-cerebrovascular causes of acute focal neurological deficits (seizure, hypoglycaemia, toxic or metabolic encephalopathies), sub-arachnoid haemorrhage, or acute and chronic subdural haemorrhage. Patients who require palliative care will not be approached.

All eligible patients will be approached by clinical research assistants (CRAs) identified in each ASU using a recruitment script. If an eligible patient agrees to participate in the study, they (or their family representative) will agree that researchers can contact them after 90 days of admission for a telephone interview; that researchers can access their medical records, and that TASC database can be accessed for their identified admissions data.

Our 90-day follow-up will comprise a computer-assisted telephone interview (CATI). One week prior to this CATI, a reminder letter will be mailed by the project officer (SD) to each participating patient. All CATIs will be undertaken by research interviewers blind to the study design and also to ASU group allocation [26,28]. These research interviewers all will have previous relevant experience and training in telephone administration of study measures. This CATI will include standard instruments as reported elsewhere in the section headed 'outcomes measures'.

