#### ASU randomisation

Once the baseline patient cohort 90-day outcome data have been collected, participating ASUs will be stratified and randomised. The project officer (SD) will first stratify ASUs according to their category classification (A or B) and then, by referring to absolute numbers of patients recruited at baseline, describe each as a 'high recruiter' or 'low recruiter'. Recruitment numbers will be included as a randomisation strata to maximise the chance of similar sample size in the intervention and control groups. Stratification details will be provided in a de-identified form to an independent statistician located offshore and not otherwise involved in the study for randomisation within strata, this will be generated using random number generating software[29]. Allocation will be based on clusters (ASUs) rather than individuals, and the sequence will be concealed until the intervention is assigned. Thus, generation of the allocation sequence and assigning of ASUs to either intervention or control group will be undertaken by the offshore independent statistician. To strengthen our methodological rigour, personnel who recruit patients (CRAs), research interviewers who undertake the CATIs, and the offshore statistician who undertakes randomisation all will be independent and also blinded to all other components of the study design. A flow diagram further outlining the trial design is shown in Figures 1 and 2.

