**Figure 2 F2:**
[figure not shown]
**CONSORT Flow diagram of the progress through the phases of the trial (part 2) **[26].

After randomisation, the FeSS intervention will be implemented at those ASUs randomised to the intervention group. Following a minimum period of three months to allow the FeSS intervention to become an integral part of usual clinical practice in the intervention ASUs, a subsequent sample of patients will be recruited from all ASUs to provide post-intervention outcome data. These data will be collected using identical tools and methods to those used to collect baseline data. For the purpose only of temporal equity, each intervention ASU will be paired with a control ASU from the same category to calibrate the timing of post-intervention data collection.

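### Baseline outcomes are collected in every ASU but given no stated role in the analysis: a recommended efficiency gain, not a flaw of validity

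*Protocol article*

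**What the plan says.** Four parts of the protocol article bear on this.

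- **Baseline cohort.** Under the patient inclusion and exclusion criteria: "To obtain baseline outcome and care data at the patient level, we will recruit a consecutive sample of English-speaking patients". Under ASU randomisation: "Once the baseline patient cohort 90-day outcome data have been collected, participating ASUs will be stratified and randomised". Every participating ASU therefore has measured 90-day outcomes before allocation. The size of this cohort is not given.
- **Post-intervention cohort.** The text after Figure 2 says that "a subsequent sample of patients will be recruited from all ASUs to provide post-intervention outcome data", and that "These data will be collected using identical tools and methods to those used to collect baseline data". The patients are different; the ASUs and the instruments are the same.
- **Analysis.** Under Data Analyses, dichotomous outcomes "will be compared between intervention and control groups using the chi-square test" and continuous outcomes "will be compared between the two intervention groups using the t-test". Stata survey commands account for clustering. For the primary outcomes only, multilevel models compare them "between groups while adjusting for potential confounders or effect modifiers and for the cluster study design".
- **Confounders.** Under Other Clinical Measures, "the following clinical measures will be used to describe and compare the groups and considered as potential confounders". The list is stroke subtype, stroke severity, pre-morbid mRS and demographic variables. The ASU's own baseline-period outcome is not on it.

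The one explicit use of baseline results in design or analysis is the recruitment count, which defines the high and low recruiter strata. Data Analyses contains no baseline covariate, period term or group-by-period term. The section on professional behaviour change says that changes in care will be determined, but no analysis of change is specified.

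**The concern.** With about nine ASUs per group, underlying ASU performance can differ noticeably between groups by chance. An ASU's earlier result on the same outcome is a natural predictor of its later result, and this design has already paid to collect it. An analysis without it has a wider confidence interval than it needs. It also invites the objection that the groups differed from the start.

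The process outcomes (glucose, temperature, swallow screening) are the most exposed. Their baseline values are collected, but they receive only two-group tests and no adjusted model.

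There is a secondary issue. With no role stated, a comparison of post-intervention results, an analysis of change and a baseline-adjusted comparison all remain open, and they can give different answers. The choice should be fixed before post-intervention data are seen.

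**Working it through.** **Inputs from the protocol (Sample Size and Table 2).** Nine ASUs per group; 520 recruited per group; 10% loss; ICC range 0.01 to 0.03, with 0.015 paired with the chosen design effect of 1.85; targets 0.5 mRS units with SD 2 (0.25 SD) and 35% versus 23%; two-sided 5%.

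**Assumptions, because the protocol gives no figure.** Baseline patients per ASU, m_b: 58 (as large as the post-intervention recruitment, 520/9) or 29 (half). Correlation c between an ASU's true level in the two periods: 0.3 to 1.0. ASUs are taken as equal in size.

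**1. The plan's own figure.** m = 520/9 = 57.8. Design effect = 1 + (57.8 − 1) × 0.015 = 1.85. 280 × 1.852 = 518, against 520 stated. It reproduces as a plain two-group comparison with no credit for baseline.

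**2. Power without baseline.** Analysed per group: 520 × 0.9 = 468, so m = 52 per ASU. The variance of an ASU mean, in SD² units, is ICC + (1 − ICC)/m. At ICC 0.015 this is 0.015 + 0.985/52 = 0.0339. Variance of the group difference = 2 × 0.0339/9 = 0.00754, SE = 0.0868, and 0.25/0.0868 = 2.88. The noncentral t with 16 df gives 77%. The same steps give 71% at ICC 0.02 and 62% at ICC 0.03.

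For 35% versus 23% at ICC 0.015: variance = (0.2275 + 0.1771) × 0.0339/9 = 0.00153, SE = 0.0391, and 0.12/0.0391 = 3.07. Power is 82%.

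**3. Power with the ASU's baseline mean as covariate.** The correlation between the two observed ASU means is

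r = ICC × c / √[(ICC + (1 − ICC)/52) × (ICC + (1 − ICC)/m_b)]

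The variance is multiplied by 1 − r², and 15 df remain. Example at ICC 0.015, c = 0.8, m_b = 58: r = 0.012/√(0.0339 × 0.0320) = 0.364, so 1 − r² = 0.867. SE = √(0.00754 × 0.867) = 0.0809, 0.25/0.0809 = 3.09, and power is 82%.

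Variance reduction, then power for 0.25 SD:

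| ICC (power without baseline) | m_b | c = 0.3 | c = 0.5 | c = 0.8 | c = 1.0 |
|---|---|---|---|---|---|
| 0.015 (77%) | 58 | 2%, 78% | 5%, 79% | 13%, 82% | 21%, 86% |
| 0.015 (77%) | 29 | 1%, 77% | 3%, 78% | 9%, 80% | 14%, 82% |
| 0.03 (62%) | 58 | 4%, 63% | 10%, 66% | 25%, 74% | 40%, 82% |
| 0.03 (62%) | 29 | 3%, 63% | 7%, 65% | 19%, 70% | 29%, 76% |

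At ICC 0.02, c = 0.8 and m_b = 58, power rises from 71% to 79%.

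**4. Chance difference in true ASU rates.** SD = √(2 × 0.35 × 0.65 × ICC/9) = 2.75 points at ICC 0.015 and 3.9 points at 0.03. The 95% ranges are ±5.4 and ±7.6 points, against a 12-point target. At ICC 0.015 and m_b = 58, baseline adjustment narrows ±5.4 to about ±4.5 (c = 0.8) or ±5.1 (c = 0.5).

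**5. Change scores.** With equal cohorts of 57.8 per ASU at ICC 0.015, r is 0.234, 0.374 and 0.468 for c = 0.5, 0.8 and 1.0. The variance factor 2(1 − r) is 1.53, 1.25 and 1.06, each worse than ignoring baseline.

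**The case against.** The strongest reply is that this is a condensed article, and that adjustment for potential confounders could include an ASU-level baseline covariate. The list under Other Clinical Measures is not declared exhaustive. That stands in part: nothing excludes baseline adjustment. But the section assigns a test to each outcome and names its candidate confounders, and for the process outcomes it states no adjusted model at all. Naming a better-specified model is a comment on the stated method, not a request for missing detail.

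Three stronger readings are tempting, and the protocol does not support them.

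- **That only post-intervention patients are analysed.** Data Analyses does not say which cohort enters the tests. This would be an inference from silence, and the statement that changes in care will be determined points, if anything, the other way.
- **That chance imbalance between ASUs undermines the result.** In a randomised comparison it causes no bias on average. The ±5.4 points are between-cluster variation that the survey and multilevel methods already carry in the standard error, and the design effect carries it in the sample size.
- **That ASU differences are left uncorrected.** Randomisation is stratified by ASU category and recruitment volume, and the primary outcomes are adjusted for case mix. What remains is residual difference in ASU baseline outcome or care.

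It is also fair to say that the gain is modest under unfavourable assumptions, and that power for 35% versus 23% is already about 82% at the planned ICC.

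**Conclusion.** The point holds as a recommended efficiency improvement. The planned cluster-adjusted comparison is valid. It forgoes precision that the design has already paid for, and some face validity, mainly for the three process outcomes.

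At the planned ICC of 0.015 the gain for a 0.25 SD target is about 1 to 8 power points over correlations of 0.5 to 1.0, and close to nil at 0.3. It is larger at ICC 0.03, about 3 to 21 points. These figures rest on an assumed baseline size and between-period correlation, equal ASU sizes and nine ASUs per group. They take no account of the stratification or case-mix adjustment, which may already capture part of the gain.

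**What to change.** In Data Analyses, state the role of the baseline cohort. Specify a multilevel model of the post-intervention cohort that includes the ASU's baseline-period result for the same outcome as an ASU-level covariate, alongside the case-mix variables. An alternative is a two-period model with a common baseline mean in both groups, random effects for ASU and ASU-by-period, and the intervention effect in the post period. Apply it to the primary outcomes and to glucose, temperature and swallow screening. Do not use change scores. Fix the choice before post-intervention outcomes are seen, and report the size of the baseline cohort.

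The cost is a change of wording and one ASU-level degree of freedom (16 to 15 with nine ASUs per group). No new data are needed and the sample size need not change.

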#### Primary hypotheses

##### Patient outcomes

1. 12% lower death or disability at 90 days post-hospital admission (disability defined as Modified Rankin Score (mRS) ≥ 2)

2. 0.25 standard deviations lower mean disability (mRS) at 90-days post-hospital admission (0.5 units on mRS scale)

3. 0.25 standard deviations lower mean dependency score at 90-days post-hospital admission (as measured by the Barthel Index)

4. 0.25 standard deviations higher mean MCS and PCS SF-36 health status scores at 90-days post-hospital admission (2.5 units for PCS; 3.5 units for MCS).

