### Outcome measures

#### Patient outcome measures

1. Death or disability at 90 days post-hospital admission. Disability will be defined as a mRS of ≥ 2 [42,43]. Our CRAs at participating ASUs will be asked to inform us when patients enrolled in the study die while in hospital. Our letter to consenting patients one week prior to the CATI will enable relatives to contact the researchers to inform us of any patient death following discharge.

2. Level of disability at 90 days post-admission using the modified Rankin Score (mRS) [42,43], a six point measuring independence rather than performance of specific tasks. The scale ranges from zero to six, where zero corresponds with no symptoms, five corresponds to severe disability, and six corresponds with death. Disability will be defined as a mRS of ≥ 2 [42].

3. Level of dependency 90 days post-hospital admission using the Barthel Index (BI) [44]. The BI measures patient performance in 10 activities of daily life. The items are divided into groups that relate to self-care (feeding, grooming, bathing, dressing, bowel and bladder care, and toilet use) and a group related to mobility (ambulation, transfers, and stair climbing). The maximal score is 100 if five-point increments are used indicating the patient is fully independent in physical functioning. The lowest score is zero, representing a totally dependent bedridden state.

4. Health status 90 days post-hospital admission using the Medical Outcomes Study Short Form 36 Health Survey Questionnaire (SF-36) [45]. The SF-36 includes a single 'health transition rating' and scores eight health domains which are aggregated to form the Physical Component Score (PCS) and the Mental Component Score (MCS). Higher mean scores reflect better states of health and wellbeing [45]. This measure of self-perceived general health status is particularly sensitive to change between one to three months following stroke [46].

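### Primary hypothesis 3 is worded against the Barthel scale, and deaths have no value on the Barthel Index or SF-36, so by default hypotheses 3 and 4 compare survivors

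*Protocol article*

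**What the plan says.** All references are to the protocol article.

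- **Primary hypotheses.** For the intervention group, hypothesis 3 predicts "0.25 standard deviations lower mean dependency score at 90-days post-hospital admission (as measured by the Barthel Index"). Hypothesis 4 predicts SF-36 component means 0.25 SD higher.
- **Patient outcome measures.** The mRS runs to six, which is death. The Barthel Index has a maximum of 100 for a fully independent patient, and at the other end: "The lowest score is zero, representing a totally dependent bedridden state". That is a living state. The SF-36 is self-perceived health, with higher scores better. Neither of these two scales is given a value for a patient who has died.
- **Patient inclusion and exclusion criteria.** The 90-day follow-up is a computer-assisted telephone interview.
- **Data Analyses.** The continuous outcomes, including the Barthel Index and the SF-36 component scores, "will be compared between the two intervention groups using the t-test", with Stata survey commands for clustering. The primary outcomes are also compared by multilevel models adjusted for potential confounders. The analysis population is given only as "Intention-to-treat analysis will applied".
- **Sample Size.** The target is "one-quarter of a standard deviation for continuous outcomes", "with 80% power and a 5% (two-sided) significance level", with 10% added for loss to follow-up.

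**The concern.** **Direction.** On a scale where 100 is independence, a lower mean is a worse result. Read literally, hypothesis 3 predicts harm from the intervention. Hypothesis 4, on a scale that also runs upwards to better health, is worded the right way round, so the two do not match.

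**Deaths.** Death is scored in hypotheses 1 and 2 but has no place on the scales of hypotheses 3 and 4. A patient who has died cannot give a telephone interview. Unless a value is assigned, that patient drops out of the t-test and of the multilevel linear model. What remains is a comparison of survivors, a group selected after randomisation by part of hypothesis 1's own outcome. The article's rationale expects survival to be open to influence: the Background names death among the consequences of aspiration.

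If the intervention keeps some severely affected patients alive, they enter the intervention mean with low scores, while their counterparts in control units are absent. A benefit could then look smaller, or even reversed, on two of the four primary hypotheses.

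**Working it through.** **1. The plan's own figures.** For the mRS the article states that "the mean hospital discharge mRS was 2, with a standard deviation of 2", so 0.5 units is 0.5/2 = 0.25 SD.

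- Patients per group: 2 × (1.960 + 0.842)² / 0.25² = 252 (stated 250).
- With 10% loss: 252/0.9 = 280 (stated 280).
- With design effect 1.85: 280 × 1.85 = 518 (stated 520).

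The sample size reproduces. No stated figure is wrong on this point.

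**2. Direction.** Hypothesis 3 has the intervention mean lower. The scale definition has lower meaning more dependent. Both cannot describe a benefit. The evident intention is lower dependency, that is, a higher Barthel mean. Because the test is two-sided, its result and the sample size are the same under either wording.

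**3. Shift in a survivor comparison.** The article gives no 90-day mortality, Barthel mean or Barthel SD, so these inputs are assumptions. Let r be the reduction in mortality, p the mortality in the intervention group, and k the number of SDs by which the extra survivors score below the other survivors. Suppose the intervention has no other effect. The extra survivors form a share r/(1 − p) of intervention survivors, so

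shift = −[r/(1 − p)] × k, in SD units.

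With control mortality 10%:

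| r | p | share r/(1 − p) | k = 1 | k = 1.5 | k = 2 | percent of 0.25 SD |
|---|---|---|---|---|---|---|
| 0.01 | 0.09 | 0.0110 | −0.011 | −0.016 | −0.022 | 4 to 9 |
| 0.03 | 0.07 | 0.0323 | −0.032 | −0.048 | −0.065 | 13 to 26 |
| 0.05 | 0.05 | 0.0526 | −0.053 | −0.079 | −0.105 | 21 to 42 |

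With control mortality 5% the extremes are −0.010 and −0.100; with 15% they are −0.012 and −0.111. The result depends mainly on r and k. If r = 0 and the same type of patient dies in each arm, the shift is 0.

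**4. One case in Barthel points.** Assume deaths of 10% (control) and 6% (intervention), other survivors with mean 80 and SD 30, and extra survivors at 20 (so k = 2).

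- Survivors: control 80.0; intervention (0.90 × 80 + 0.04 × 20)/0.94 = 77.45. Difference −2.55 points, or −0.085 SD, although no patient did worse.
- Deaths scored 0: control 0.90 × 80 = 72.0; intervention 0.90 × 80 + 0.04 × 20 = 72.8. Difference +0.8 points.

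The sign depends on how deaths are handled.

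**5. Effect on the SD.** With the control figures above and deaths at 0, the variance is 0.90 × 30² + 0.90 × 0.10 × 80² = 810 + 576 = 1,386, so the SD is about 37.2 instead of 30. A quarter of an SD becomes 9.3 points instead of 7.5.

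**The case against.** **The article never restricts these comparisons to survivors.** A reader might infer that it lays down a survivor analysis. It does not. That is what happens if the text is followed with nothing added, and a scoring rule such as Barthel 0 for death could stand in a full protocol or analysis plan not shown here. This objection stands as far as it goes. It does not dispose of the point, because the article itself fixes the primary status of these outcomes, the two analyses, the scale ranges and intention to treat, and those do not fit together for a patient who dies.

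**The bias may be trivial.** A reader might infer that any effect on mortality spoils the result. The table does not support that: a 1-point reduction with k = 1 gives 4% of the target. The 10% versus 6% case needs a 40% relative reduction in deaths and extra survivors 2 SD below the rest. Patients needing palliative care are not approached, which should lower mortality among those enrolled. The multilevel model may adjust for stroke severity, listed as a potential confounder, and so absorb part of the shift. All this limits the size.

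**Death is already counted where it matters most.** Hypothesis 1 includes death and hypothesis 2 scores it as 6, so a survival benefit counts in the right direction in both. This is true, but hypotheses 3 and 4 are also declared primary and will be read in their own right.

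**Power.** A reader might infer that the trial is underpowered for these outcomes because the 10% allowance omits deaths. The article does not say whether the 10% includes them; if it does, nothing changes. If another 10% die, 520 × 0.9 × 0.9 = 421 patients remain per group, or 46.8 per unit. The design effect is then 1 + 45.8 × 0.015 = 1.69, the effective size 421/1.69, about 250, and power 79.8%, which is the planned level. Holding the design effect at 1.85 gives 76.0%, but that ignores the smaller clusters.

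**The direction error is only wording.** That is correct: no analysis changes.

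**Conclusion.** The point holds in two parts of different strength.

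The wording error in hypothesis 3 is certain from the article's own text and has no numerical consequence. A reader might infer that the test itself is set up the wrong way; being two-sided, it is not.

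The handling of deaths is a real weakness, inferred from what the article fixes and not from any stated rule. Followed as written, both the t-test and the multilevel linear model for the Barthel Index and SF-36 rest on survivors. The resulting shift is 0.011 to 0.105 SD against the intervention, under assumed 10% control mortality, a reduction of 1 to 5 points and extra survivors 1 to 2 SD lower. None of those inputs comes from the article. The shift is negligible at the bottom of the range, material at the top, and would favour the intervention if it raised mortality among severely affected patients. Hypotheses 1 and 2 are untouched.

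The article's figures do not establish a loss of power. Nor does the point require SF-36 to lose its primary status; that would be a preference.

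**What to change.** - **Hypothesis 3.** State the expected benefit as a Barthel Index mean 0.25 SD higher in the intervention group.
- **Barthel Index.** In both the t-test and the multilevel model, include patients who died at the worst score (0), or use an equivalent ranking that places death last. Give the survivor comparison as a sensitivity analysis.
- **SF-36.** Label the comparison as one among survivors, and report it beside the number of deaths in each group.
- If a rule for deaths already exists in another trial document, one sentence stating it settles the second part, provided it applies to both analyses.

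**Cost.** Some wording and one additional Barthel analysis. Scoring death as 0 makes death and total dependency indistinguishable on that scale. It also changes the SD behind the 0.25 SD target (from 30 to about 37 points in the illustration above), so the target should be restated for the death-inclusive score.
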